## Intervention

### Description of intervention

The resistance exercise regime consists of ten, home-based, physical exercises as illustrated in an accompanying leaflet. Each exercise is to be repeated ten times in one minute, increased to fifteen times per minute after about 1 month, when comfortable. A break of 30 seconds is to be taken between sets of exercises. Exercises are to be undertaken at least four times per week and up to every day. Participants should also walk for 30 to 45 minutes, three to four times per week. Participants are advised to consume 1.2 g protein per kg body weight each day. A leaflet will be provided with information on sources of protein, amounts of protein per typical serving and suggested meals. A sample exercise leaflet and protein dietary guidance are shown in
Figure 4 and
Figure 5.

**Figure 4. f4:**
[figure not shown]
Sample exercise leaflet.

**Figure 5. f5:**
[figure not shown]
Sample dietary protein guidance leaflet.

## Safety reporting

Participants are asked not to undertake any exercise that causes pain and to discontinue the exercise regime if they have any concern, injury or physical signs constraining participation. Safety will be evaluated throughout the study by recording adverse events (AEs), and inviting participants to attend for assessment of vital signs and physical exam, should they contact their GP with any concerns.

### Definitions

***AE*.** Any untoward medical occurrence in a participant and which does not necessarily have a causal relationship with this intervention. An adverse event can therefore be any unfavourable and unintended sign, symptom or disease, whether or not considered related to the intervention.

***Serious AE (SAE)***

Any untoward medical occurrence or affect that:

-   results in death,

-   is life-threatening*,

-   requires hospitalisation or prolongation of existing hospitalisation,

-   results in persistent or significant disability or incapacity,

-   is a congenital anomaly or birth defect

-   important medical events**

*Regarding a life-threatening event, this refers to an event in which the subject was at risk of death at the time of the event; it does not refer to an event which hypothetically might have caused death if it were more severe.

**Some medical events may jeopardise the subject or may require an intervention to prevent one of the above characteristics/consequences. Such events (hereinafter referred to as ‘important medical events’) should also be considered as ‘serious’ in accordance with the definition

***Severity of AEs*.** The term ‘severity’ is used here to describe the intensity of a specific event. This has to be distinguished from the term ‘serious.

### Evaluation of AEs and SAEs

***Assessment of seriousness*.** The investigator should make an assessment of seriousness.

***Assessment of casualty*.** The investigator/sponsor must make an assessment of whether the AE/SAE is likely to be related to the intervention according to the following definitions:

Unrelated

Where an event is not considered to be related to the study intervention.

Possibly

Although a relationship to the study intervention cannot be completely ruled out, the nature of the event, the underlying disease, or temporal relationship make other explanations possible.

Probably

The temporal relationship and absence of a more likely explanation suggest the event could be related to the study intervention.

All AEs/SAEs judged as having a reasonable suspected causal relationship (e.g. possibly, probably) to the study intervention will be considered as ARs/SARs.

All AEs/SAEs judged as being related (e.g. possibly, probably) to an interaction between the study medication and another medication will also be considered to be ARs/SAR.

Alternative causes such as natural history of the underlying disease, concomitant therapy, other risk factors and the temporal relationship of the event to the treatment should be considered.

***Assessment of severity*.** The investigator will make an assessment of severity for each AE/SAE and record this on the CRF according to one of the following categories:

Mild

An event that is easily tolerated by the subject, causing minimal discomfort and not interfering with everyday activities.

Moderate

An event that is sufficiently discomforting to interfere with normal everyday activities.

Severe

An event that prevents normal everyday activities.

### Reporting procedures for all adverse events

All AEs occurring during the study observed by the investigator or reported by the subject, whether or not attributed to the study medication, will be documented.

The following information will be recorded: description, date of onset and end date, severity, assessment of relatedness to the study intervention, other suspect medication or device and action taken. Follow-up information should be provided as necessary.

AEs considered related to the study intervention as judged by an investigator will be followed until resolution or until the event is considered stable. All related AEs that result in a subject’s withdrawal from the study or are present at the end of the study, should be followed up until a satisfactory resolution occurs.

It will be left to the investigator’s clinical judgment whether or not an AE is of sufficient severity to require the subject’s removal from the study. A subject may also voluntarily withdraw due to what he or she perceives as an intolerable AE. If either of these occurs, the subject must undergo an end-of-study assessment and be given appropriate care under medical supervision until symptoms cease or the condition becomes stable.

The severity of events will be assessed on the following scale: mild, moderate, severe.

The relationship of AEs to the study intervention will be assessed by the investigator.

### Reporting procedures for serious adverse events

The investigator will report all serious adverse events immediately to the supervisor. The immediate report will be followed by detailed, written reports. The immediate and follow-up reports will identify subjects by unique code numbers assigned to the latter.

The immediate report will be made by the investigator within a very short period of time and under no circumstances should this exceed 24 hours following knowledge of the serious adverse event.

The supervisor will keep detailed records of all adverse events which are reported to her by the investigator or investigators.

## Statistics

### Description of statistical methods

Final analysis of the trial will be performed by the independent trial statistician after end-of-trial.

### Determination of sample size subjects

We have calculated a sample size of 176 with the following parameters: Two independent study groups (i.e., control and intervention); outcome measure of frailty status (i.e., change from frail or pre-frail to non-frail as measured by SHARE-FI); improvement of frailty status in the intervention group to non-frail of 15%, allowing for a 3% improvement in the control group due to bias; enrolment ratio of 1; probability of type I error of 5% (0.05); power 80%. Enrolment of 210 participants assumes a 15% drop out rate.

Sample sizes in comparable trials include Binder, J Am Geriat Soc 2002 (sample size 115)
^20^, Liu, Clin Rehab 2017 (sample size 79)
^21^ and Serra-Prat, Age Aging 2017 (sample size 172)
^2^. The average study size of the 31 studies included in our meta-analysis of frailty interventions
^7^ was exactly 100.

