**Figure 1. f1:**
[figure not shown]
Conceptual framework of the different frailty operationalisations used in this study.

Recruitment based CFS seems the most inclusive, but baseline measures will be obtained of all measures at baseline and follow up.

This study provides an opportunity to share an optimised intervention with community-dwelling adults aged 65 and over, whose baseline CFS is not worse than mild (i.e. 5 or less), evaluate improvements in health outcomes and demonstrate how the intervention may be incorporated efficiently in clinical practice. The results are intended to encourage mainstream adoption of practical interventions to reverse clinical frailty and build resilience in primary care.

An intervention with ten recommended resistance exercises and dietary guidance on protein consumption has been derived from findings of our systematic review
^6^ and meta-analysis
^7^ and optimised through a patient and public involvement (PPI) process.

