***Inclusion criteria***

 Aged 65 or older at baseline Rockwood clinical frailty scale score 4 or 5 (vulnerable or mildly frail) Able and willing to provide informed consent and to comply with the requirements of this study protocol

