### Analysis sets

Final analysis for this trial will be conducted on the intention-to-treat population, which will include all subjects randomised to the treatment arms. Sensitivity analysis will be conducted on the per protocol population (full analysis set), which will include all subjects that attend all study visits and have complied with the intervention.

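### The 80% power counts moves to non-frail on SHARE-FI, but entry is by CFS, with no allowance for participants already non-frail on SHARE-FI and no stated denominator for the 15% and 3%

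*Protocol article*

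**What the plan says.** **Sizing.** The section on determination of sample size takes as its outcome a "change from frail or pre-frail to non-frail as measured by SHARE-FI". It assumes 15% in the intervention arm, "allowing for a 3% improvement in the control group due to bias", an "enrolment ratio of 1", type I error 5% and power 80%. The result is 176, raised to 210 for 15% dropout. The section does not say whether 15% and 3% are proportions of everyone analysed or of those who start frail or pre-frail.

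**Entry.** The inclusion criteria ask for "Rockwood clinical frailty scale score 4 or 5 (vulnerable or mildly frail"), and the exclusion criteria remove CFS above 5. No criterion uses SHARE-FI, which is only measured at baseline. The rationale describes physical frailty as narrower than what CFS captures, and the text after Figure 1 explains the choice of entry scale: "Recruitment based CFS seems the most inclusive".

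**Analysis.** The final analysis uses the "intention-to-treat population, which will include all subjects randomised to the treatment arms". For the primary endpoint, the efficacy section gives a chi-square test on changes in the proportions non-frail, pre-frail and frail. It also gives a linear mixed model on the SHARE-FI score with baseline SHARE-FI and age as fixed effects and practice as a random effect.

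**The concern.** The sizing event, the entry rule and the analysis set do not refer to the same people. A participant with CFS 4 or 5 who is already non-frail on SHARE-FI is eligible and is analysed, but cannot have the event. The protocol deliberately chose the more inclusive scale for entry, so such participants are to be expected in principle, yet the calculation neither mentions them nor allows for them.

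Two things are at stake. First, by the plan's own method the calculation has no reserve at 176, so any participants who cannot respond lower the power if 15% and 3% are rates among those at risk. Second, if the chi-square test compares three-month categories in everyone, participants who were non-frail from the start count as non-frail in both arms. They then hide the contrast that the trial was sized to detect.

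**Working it through.** **Inputs.** From the sample size section: p1 = 0.15, p2 = 0.03, 1:1, alpha 0.05 (sidedness not stated; two-sided fits), power 80%, 176 evaluable, 210 enrolled, 15% dropout. Assumed, because the document gives no figure: q, the share of evaluable participants who are non-frail on SHARE-FI at baseline, varied from 0 to 40%.

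**1. Reproduce the plan's figure.** With the pooled two-sided formula and no continuity correction,

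n per arm = [1.96·√(2·p̄(1−p̄)) + 0.8416·√(p1(1−p1) + p2(1−p2))]² / (p1−p2)², with p̄ = 0.09.

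- √(2·0.09·0.91) = 0.4047 and √(0.1275 + 0.0291) = 0.3957.
- n = (0.7932 + 0.3331)² / 0.0144 = 88.09 per arm, that is 176 rounded to the nearest or 178 rounded up.
- Power at 88 per arm = Φ[(0.12·√88 − 0.7932)/0.3957] = Φ(0.840) = 79.96%.
- Dropout: 176/0.85 = 207.1 and 178/0.85 = 209.4, so 210 is consistent.

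The stated size is correct for its inputs. All of the 15% inflation goes to dropout.

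**2. Power if 15% and 3% are rates among those at risk.** The power formula is Φ[(|p1−p2|·√n − 1.96·√(2p̄(1−p̄)))/√(p1(1−p1)+p2(1−p2))]. It is applied in two ways:

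- (A) everyone stays in the denominator: rates 0.15(1−q) and 0.03(1−q), n = 88 per arm;
- (B) only those at risk are analysed: rates 0.15 and 0.03, n = 88(1−q) per arm.

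| q | A | B |
|---|---|---|
| 0 | 80.0% | 80.0% |
| 5% | 77.6% | 77.9% |
| 10% | 75.1% | 75.6% |
| 20% | 69.6% | 70.5% |
| 30% | 63.2% | 64.6% |
| 40% | 56.2% | 57.9% |

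Example, A at q = 20%: rates 0.12 and 0.024; Φ[(0.096·9.381 − 0.7165)/0.3592] = Φ(0.512) = 69.6%.

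*Sensitivity to the approximation.* Exact binomial enumeration of the uncorrected chi-square test gives higher values. For q = 0/10/20/30/40%, A is 83.5/78.5/72.2/64.8/56.4%, and B (rounded to 88/79/70/62/53 per arm) is 83.5/80.2/75.0/69.1/60.8%. The pattern is the same, but at q of 10% or less the shortfall against 80% is small or absent.

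**3. Power if 15% and 3% are rates among all analysed and transitions are counted.** Nothing changes: 79.96% at any q. At q = 20% the at-risk rates would then be 0.15/0.8 = 18.75% and 0.03/0.8 = 3.75%.

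**4. Power if the chi-square compares the proportion non-frail at three months in everyone.** Assume also that 90% of the baseline non-frail stay non-frail in both arms (not in the document). At q = 10%:

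- At-risk rates: 0.09 + 0.9·0.15 = 0.225 v 0.09 + 0.9·0.03 = 0.117; power 48%. Setting the retention at 50% instead gives 57%, and at 100% gives 46%.
- All-analysed rates: 0.09 + 0.15 = 0.24 v 0.09 + 0.03 = 0.12; power about 55%.

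On this reading power falls below 80% whichever denominator was meant.

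**The case against.** A reader might infer that the trial does not have its stated 80% power. The document does not support that as a fact. It gives no figure for q, and calling physical frailty a narrower concept does not say how many CFS 4–5 patients are non-frail on SHARE-FI. Pre-frail status is enough to be at risk, and the trial design section describes the population as pre-frail and mildly frail, although it ties this to no scale. The sample size section also leaves the denominator open: if 15% and 3% already refer to everyone analysed, a transition analysis keeps 80% at any q. All of this stands, and it makes the power loss conditional.

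A reader might also take the figure of about 48% as the trial's real power. That needs a three-month cross-sectional reading of the chi-square test, an assumed retention, and no treatment effect in people who start non-frail. The efficacy section speaks of changes in proportions, which can mean transitions. An intervention meant to delay frailty could also help those who start non-frail. The figure therefore only illustrates one reading.

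Finally, the baseline-adjusted mixed model on the score is already planned, and participants who start non-frail are informative in it. That is a real mitigation. However, the 80% was calculated for the binary event, and no power is stated for the score.

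None of this removes the mismatch: the event, the entry rule and the analysis set are all fixed in the protocol, and no text connects them.

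**Conclusion.** The point holds in conditional form. The 176 and the 210 reproduce, but the 80% is secured only if every evaluable participant is frail or pre-frail on SHARE-FI at baseline, or if 15% and 3% are rates among all analysed and the analysis counts transitions. The protocol establishes neither.

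If the rates apply to those at risk, power by the plan's own method is about 78%, 75–76%, 70–71%, 63–65% and 56–58% for q of 5, 10, 20, 30 and 40%. The loss is modest up to about 10% and material from about 20%. If three-month categories are compared in everyone, power is lower still, about 48% at q = 10% with 90% retention. The conclusion rests on q, which is assumed throughout, and on which denominator and which form of the chi-square comparison were intended.

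The differing descriptions of CFS at entry are a separate matter. The text after Figure 1 speaks of adults "whose baseline CFS is not worse than mild (i.e. 5 or less"), and the abstract and primary objective are similarly wide, whereas the inclusion criteria require 4 or 5. These sections should be reconciled, but the power argument does not depend on it.

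**What to change.** No additional patients are needed.

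1. **Sample size section.** State whether 15% and 3% are proportions of all analysed or of those frail or pre-frail on SHARE-FI at baseline. Present the 80% as conditional on that, and give power over a range of baseline non-frail shares, for example as tabulated above.
2. **Efficacy section, categorical analysis.** Define it as the proportion non-frail at three months among participants frail or pre-frail on SHARE-FI at baseline, compared between arms with adjustment for baseline category, in place of the unadjusted chi-square test. Baseline SHARE-FI is already collected, and a subset defined by a baseline measurement keeps the randomised comparison.
3. **Efficacy section, score analysis.** Keep the baseline-adjusted mixed model on the SHARE-FI score as the analysis that uses everyone randomised, and say that no power has been stated for it.

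The cost is a change of wording and a less favourable stated power. Restricting the categorical analysis to those at risk does not bring power back to 80% by the plan's method (column B). It makes the analysis match the event on which the trial was sized and avoids the larger loss of the three-month comparison in everyone.

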### Analysis sets

Final analysis for this trial will be conducted on the intention-to-treat population, which will include all subjects randomised to the treatment arms. Sensitivity analysis will be conducted on the per protocol population (full analysis set), which will include all subjects that attend all study visits and have complied with the intervention.

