### Feasibility study

Feasibility of the exercise component of the intervention was assessed in a study in 2019 and 2020
^12^. The findings have been key to refining the intervention for this RCT. We offered an exercise intervention to reverse frailty and build resilience in primary care consultations. We set out to assess uptake of the exercise regime; ratings of its ease and subjective health after participation; how a follow-up telephone-call might affect compliance and overall feasibility. We applied the Bowen feasibility model
^13^ which has been successfully used in assessing public health and preventive medicine interventions. This feasibility model tests eight areas of focus: acceptability; demand; implementation; practicality; adaptation; integration; expansion; and limited-efficacy testing. Selected results include:

A total of 94 of 107 eligible people (88%) participated (average age 77, 59 females (63%)). 95% of females and 78% of males enrolled. Only 15% had previously considered resistance exercises.

Participants found the exercises both easy to follow and generally easy to do. Overall, 32% described exercises as ‘very easy’, 55% ‘somewhat easy’, 7% ‘neither easy nor hard’, 6% ‘somewhat hard and 0% ‘very hard’.

At one month, 66% of participants called were exercising regularly (76% of females, 50% of males). At two months, compliance among those who had not been called at one month was: 65% (67% of females, 62% of males). However, compliance among those previously called was higher: 78% (88% of females, 63% of males). 64% of those who were not doing exercises at one month had taken them up following the single phone call (67% of females, 63% of males).

Many described how the home-based exercises helped with staying active and reducing anxiety while housebound during the Covid-19 pandemic

The majority of participants self-reported their general health had improved as a result of doing the exercises and none reported feeling worse. 14% felt ‘much better’, 52% ‘slightly better’, 34% ‘about the same’, 0% ‘slightly worse’, and 0% ‘much worse’

Each of the eight areas of focus of the Bowen feasibility model have been addressed and satisfy overall feasibility. Publication of this feasibility study is pending.

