### Study methods, assessments and procedures

GP site investigators will undergo three team-based training sessions prior to enrolment, monthly meetings after enrolment and additional ad-hoc meetings when required, led by the principal investigator, in order to standardise the approach and align to this study protocol, including patient communication, intervention delivery and data gathering and management.

Adults attending a GP surgery, meeting the eligibility criteria, will be offered general information about the study by the attending GP. If interested and willing to consent, they will be offered an information leaflet for the trial, and invited to participate. Participants will be randomly assigned to ‘intervention’ or ‘usual care’ parallel arms.

Participants randomly assigned to the usual care group will receive normal primary care, including physical rehabilitation if needed.

Intervention participants will be provided a leaflet with strength exercises and a discussion on how strength exercises have been shown to delay and reverse frailty and build resilience. The information leaflet will have a photographic overview of a home-based exercise regime. They will also be provided with information on post exercise protein consumption as part of a normal balanced diet.

Baseline measurements for all recruited patients will be: age, sex, education, living arrangement (alone, with others), smoking status, alcohol intake, blood pressure, heart rate, BMI (weight and height), comorbidities, malnutrition universal screening tool (MUST), CFS, SHARE-FI (which includes handgrip strength) and bioelectrical impedance for muscle mass, body fat, bone weight, base metabolic rate and ‘biological age’. Bioelectrical impedance will be measured using a Tanita RD 545 Segmental Body Composition Analyser, with dual frequency technology and medical grade accuracy.

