Intervention participants will be called after one month and after three months by the GP and asked if they had followed the exercise regime (and for how long and how many times a week) and dietary guidance. At three months they will be asked if they found the exercises ‘very easy’, ‘somewhat easy’, ‘neither easy nor hard’, ‘somewhat hard’, or ‘very hard’; and had they noticed any subjective difference to their health as a result of the intervention, namely feeling ‘much better’, ‘slightly better’, ‘about the same’, ‘slightly worse’ or ‘much worse’. All participants will be invited to return at three months for a clinical assessment and measurement of health indicators and frailty status as described above by the GP. Participants will be invited to return for subsequent one year follow up appointments. This 12-month follow up will be subject to a further ethics committee review. The follow up visits will be free of charge. A schedule of events for baseline, one-month call and three months follow up are shown in
Figure 3.

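### The per-protocol set is mislabelled as the full analysis set and is defined by compliance with an intervention that only one arm receives, so the sensitivity contrast is not protected by randomisation

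*Protocol article*

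**What the plan says.** The Analysis sets section of the protocol article names two populations. The main one is clear: "Final analysis for this trial will be conducted on the intention-to-treat population, which will include all subjects randomised to the treatment arms". The second, used for sensitivity analysis, is the "per protocol population (full analysis set), which will include all subjects that attend all study visits and have complied with the intervention".

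The section on study methods, assessments and procedures shows how each criterion falls on the two arms:

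- **Usual care:** "Participants randomly assigned to the usual care group will receive normal primary care, including physical rehabilitation if needed". No study regimen is given to this arm.
- **Compliance data:** "Intervention participants will be called after one month and after three months by the GP and asked if they had followed the exercise regime". Frequency and duration of exercise are also asked about, as is the dietary guidance. No such call is described for usual care.
- **Attendance:** "All participants will be invited to return at three months for a clinical assessment and measurement of health indicators and frailty status". This applies to both arms.

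Three other sections bear on the point. The section on discontinuation and withdrawal requires withdrawal for lack of compliance with the study or its procedures, in either arm. Safety reporting asks participants to stop exercising if they have concerns, an injury or physical limits. The Feasibility study section gives the only adherence figures.

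**The concern.** There are two faults in one sentence. First, a full analysis set is by convention as close as possible to everyone randomised. The same section gives that role to the intention-to-treat population, so the term cannot also name a set of compliant completers.

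Second, the compliance condition has no counterpart under usual care. Read literally, no usual-care participant complied with the intervention and that arm is empty. Read sensibly, the condition filters the intervention arm alone, after randomisation. Adherent attenders are then compared with all attending controls, including controls who would not have adhered had they been offered the programme.

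This is the only sensitivity analysis the article names. If it agrees with the intention-to-treat result, readers may take that as confirmation, when part of the agreement could come from who was removed.

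**Working it through.** **Plan's own figure.** The sample size section gives 15% v 3%, alpha 0.05 (two-sided assumed) and 80% power. With pooled variance and mean proportion 0.09:

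n per arm = [1.96 × √(2 × 0.09 × 0.91) + 0.842 × √(0.15 × 0.85 + 0.03 × 0.97)]² / 0.12² ≈ 88.1, rounded up to 89, or 178 in total.

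The plan's 176 is 88 per arm, with power 0.7996. For dropout, 176 / 0.85 = 207.1, or 208 for equal arms, against 210 planned. The figure reproduces and is not in dispute.

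**Who is left in the per-protocol set.** 210 randomised gives 105 per arm, and 105 × 0.85 ≈ 89 attend in each arm. The Feasibility study section reports 66% exercising regularly at one month. At two months it reports 65% among those not called earlier, while "compliance among those previously called was higher: 78" per cent. Every intervention participant in this trial is called at one month, so 78% is the closest figure.

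- 78%: 89.25 × 0.78 ≈ 70 intervention v 89 usual care
- 66%: 89.25 × 0.66 ≈ 59 v 89
- 65%: 89.25 × 0.65 ≈ 58 v 89

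**Bias with no treatment effect.** Let f be the share of intervention attenders removed. Let d be the amount by which non-adherers would do worse in either arm, in SD units, after adjustment for baseline SHARE-FI and age, as in the primary model. Usual care retains both types and the intervention arm only adherers, so bias = f × d. With SE = √(1/n₁ + 1/89), the two-sided rejection probability is P(Z > 1.96 − bias/SE) + P(Z < −1.96 − bias/SE). The documents do not give d; 0.3 to 0.5 is an assumption.

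| Adherence | f | d | Bias (SD) | n₁ | SE | Rejection |
|---|---|---|---|---|---|---|
| 78% | 0.22 | 0.3 | 0.066 | 70 | 0.160 | 7.0% |
| 78% | 0.22 | 0.5 | 0.110 | 70 | 0.160 | 10.6% |
| 66% | 0.34 | 0.3 | 0.102 | 59 | 0.168 | 9.3% |
| 66% | 0.34 | 0.5 | 0.170 | 59 | 0.168 | 17.3% |

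**Same check on the binary outcome.** Let c be adherence, p the overall recovery rate to non-frail, and RR the ratio of adherers' to non-adherers' recovery rates (assumed). The per-protocol intervention rate is p × RR / (c × RR + 1 − c), against p in usual care. With p = 0.15:

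- c = 0.78: bias 0, +1.2, +1.9 and +2.6 percentage points at RR 1, 1.5, 2 and 3
- c = 0.65: bias 0, +2.0, +3.2 and +4.6 points

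With p = 0.03 the bias is at most +0.9 points. RR below 1 would reverse the sign.

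**The case against.** The strongest reply is that direction and size are assumed. Nothing in the documents links adherence to prognosis. Feasibility adherence differed by sex (76% of females and 50% of males at one month), which shows selection but not its sign. The instruction to stop exercising for injury or physical limits makes bias towards the intervention plausible without proving it. This stands: a reader might infer that the analysis is biased towards the intervention, and the documents support only that it can be, and probably would be.

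Several further points also stand:

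- A reader might infer that a favourable per-protocol result is to be expected even with no effect. The figures above do not show that: 83 to 93% of such trials would not reject.
- The 17% figure needs the 66% one-month rate; 78% fits the trial's call schedule better. The feasibility study tested exercise only, to two months, so adherence at three months is unknown.
- Dropout and non-compliance are treated as independent losses. If dropouts are mostly non-adherers, fewer attenders are removed and the bias is smaller.
- Attendance is required in both arms, so the comparison is with attending controls, not all controls.
- The fear that the two populations could be swapped in reporting is weak. Both are defined in words, and the section on baseline characteristics uses only the intention-to-treat and per-protocol names.
- A statistical analysis plan, not shown, may add other sensitivity analyses and a compliance threshold. The absence of a threshold here is not counted.

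The reply does not remove the wrong label or the one-sided criterion. Both are stated in this document.

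**Conclusion.** The point holds in a limited form. The label is wrong, and the compliance criterion can work in one arm only. It would remove about 22% of intervention attenders at the closest feasibility rate, up to about 35%, and no usual-care attenders. Randomisation does not protect the resulting contrast.

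If non-adherers would do 0.3 to 0.5 SD worse after adjustment, bias under no effect is about 0.07 to 0.11 SD, with 7 to 11% rejection at 78% adherence. The upper case, at 66%, is 0.17 SD and 17%. If adherence is unrelated to prognosis the bias is zero. The calculation ignores variation between practices.

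A reader might go on to infer that the trial's main conclusion is compromised. It is not: the final analysis is by intention to treat on all randomised, and the defect is confined to the sensitivity analysis and the per-protocol descriptive tables. It is worth correcting because it is cheap to fix and because agreement between the two analyses could be over-read.

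**What to change.** 1. Delete the words in brackets that call the per-protocol set a full analysis set.
2. If a per-protocol table is kept, label it descriptive, apply the visit criteria identically in both arms, and do not present it as a robustness check of the intention-to-treat result.
3. Add a supplementary complier-average causal effect estimate on all randomised, with arm as the instrument and the same covariates as the primary model (baseline SHARE-FI, age, practice). Define adherence in advance from the frequency and duration recorded at the one- and three-month calls.
4. State the limits of that estimate. Its confidence interval is wider, adherence is self-reported, and its test of no effect is essentially the intention-to-treat test. The education, dietary advice and GP calls may act on people classed as non-adherent, which strains the assumption that allocation works only through adherence.
5. Reconcile the withdrawal rule for lack of compliance with the intention-to-treat set, so that three-month outcomes are still collected on non-adherers. Steps 3 and the main analysis both need them.

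The cost is a few words in the protocol and one extra model on data already planned. Steps 1, 2 and 5 stand even if the sponsor declines step 3.
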